**Methods:**

Intended for use after classroom training occurs, the mobile app has three primary functions designed to increase behavioral intent to deliver SBIRT: (1) review skills (ie, address knowledge and beliefs about SBIRT), (2) apply skills with patients (ie, build confidence and perceived behavioral control), and (3) report performance data (ie, increase accountability and social norms and/or influence). The app includes depression and anxiety screening tools due to high comorbidity with substance use. A randomized controlled trial (RCT) is in progress among health and social service learners (N=200) recruited from 3 universities and 6 different training programs in nursing, social work, internal medicine, psychiatry, and psychology. Participants are randomized to SBIRT classroom instruction alone or classroom instruction plus app access prior to beginning their field placement rotations. TPB-based data are collected via Qualtrics or via the mobile app pre-post and SBIRT utilization, weekly for 10 weeks. Key outcomes include the frequency of and self-reported confidence in delivery of SBIRT.

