Theoretical models identifying barriers and facilitators regarding learning and skill translation may help guide the development of intervention strategies to enhance skill transfer and implementation. On the level of individual provider (or learner) behavior, the theory of planned behavior (TPB) provides a well-validated, conceptual model that identifies both internal and external key factors that could influence SBIRT skill translation [40]. In the TPB model, behavioral intent (to perform the behavior of interest) is determined by attitudes and/or beliefs about the behavior, perceived social norms, and perceived behavioral control. The TPB is contextualized for SBIRT skill translation in Figure 1, allowing us to assess learners on each of these variables and to provide matched interventions as needed to promote SBIRT usage. For example, we provide information on the extent of substance use and related problems, and SBIRT efficacy to shape attitudes regarding the value of screening and treatment. We provide information on standards of care (eg, that SBIRT has been recommended by the US Preventive Task Force and many health professional bodies) to influence perceived social norms. Moreover, we provide tools to support practicing SBIRT to positively impact both attitudes and perceived behavioral control such as trainees’ confidence in successfully performing SBIRT and integrating it into clinical care.

The aim of this paper is to describe the process of TPB-based mobile alcohol and drug SBIRT app development, beta testing, and protocol for a randomized controlled trial (RCT) comparing health professional learners with access to the app (intervention arm) to learners without access to the app (control arm). We hypothesize that participants in the intervention arm will be more likely to deliver SBIRT in clinical placements than those in the control arm and will be more likely to report intention to deliver SBIRT in the future. We also hypothesize that intervention participants will report more positive beliefs about SBIRT, greater knowledge, and greater perceived control over SBIRT delivery in clinic.

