#### Data Collection

At baseline, all participants answer a TPB-based questionnaire via Qualtrics (control) or directly on the app (intervention). At the end of each week, all participants are asked to respond to a brief Qualtrics survey about how often they used SBIRT either by text message (short message service, SMS) or by email. Upon completion of their clinical rotation, all learners are asked to repeat the original TPB-based questionnaire and to provide general feedback about either the app usage (intervention) or their general satisfaction with SBIRT (control).

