### Intervention

#### Design and Function

The SBIRT app has the following three primary functions to address TPB concepts: (1) Review SBIRT skills (to help change beliefs and attitudes), (2) Apply SBIRT skills in clinic practice (to help impact attitudes, perceived behavioral control), and (3) Report SBIRT use (to report norms, as well as study outcomes). A fourth component, the Tools section, includes additional reference material and links (Figure 3). After downloading the app, intervention learners create an account and complete the pre-TPB survey. Immediate TPB results are given to the learners along with tailored recommendations on what they should do next. For example, if learners score low on SBIRT knowledge, they are directed to the Review section. A progress checklist in the Tools section reminds them of “homework” they still need to complete. Throughout the study intervention learners are reminded to use the app via the weekly SBIRT usage surveys and periodic text messages promoting app usage.

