### Analyses

Analyses will be conducted using SAS (SAS Institute Inc., 2011). Descriptive statistics, including distributions, means, standard deviations, skewness, and kurtosis will be obtained for all variables. Continuous measures will be tested for normality and homogeneity of variance. If the distribution is normal, Likert-scale responses will be analyzed as continuous scores [53]. Chi-square tests, student *t* tests, and analysis of variance (ANOVA) tests will be used to determine inclusion in multivariate regression models. Bivariate analyses will examine rate of SBIRT delivery in the two arms and comparison of TPB-based measures (eg, beliefs about SBIRT, social norms and influence, and perceived behavioral control). Multivariate analyses (logistic and multiple regression) will examine the impact of these factors on SBIRT delivery.

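### The delivery regression does not exclude the 10-week TPB scores; if they enter beside arm, its arm coefficient is not the randomized effect of the app

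*Protocol article*

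**What the plan says.** The Analyses section describes three steps.

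- Covariate entry is decided by testing: chi-square, t and "analysis of variance (ANOVA) tests will be used to determine inclusion in multivariate regression models".
- Delivery and TPB are each compared by arm: "Bivariate analyses will examine rate of SBIRT delivery in the two arms and comparison of TPB-based measures".
- Delivery is then modelled: "Multivariate analyses (logistic and multiple regression) will examine the impact of these factors on SBIRT delivery".

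No other multivariable model for delivery is described. The section does not say whether baseline, 10-week or change scores are used, or whether arm is a term.

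Elsewhere the article gives the TPB measures two further roles.

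- They are the mechanism. The Introduction states that "behavioral intent (to perform the behavior of interest) is determined by attitudes and/or beliefs about the behavior, perceived social norms, and perceived behavioral control". The Abstract says "the mobile app has three primary functions designed to increase behavioral intent to deliver SBIRT", and Design and Function says "The SBIRT app has the following three primary functions to address TPB concepts".
- They are outcomes. The Introduction hypothesizes that "intervention participants will report more positive beliefs about SBIRT, greater knowledge, and greater perceived control over SBIRT delivery in clinic".

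On timing, Table 1 has delivery reported weekly and TPB measured at baseline and 10 weeks. Data Collection places the second measurement at the end: "Upon completion of their clinical rotation, all learners are asked to repeat the original TPB-based questionnaire".

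**The concern.** A variable that the app is meant to change, and that is recorded only after the outcome has accrued, is not a legitimate adjustment variable for the app's effect on that outcome. With 10-week TPB beside arm, the arm coefficient answers a different question: what the app does other than through the TPB constructs, and only if no common causes or feedback are present.

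The TPB coefficients have their own problem. Learners who delivered SBIRT often may report more confidence because they did so. A coefficient presented as the impact of TPB on delivery could therefore run the wrong way in time.

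The screening rule adds to the risk. A TPB measure that the app has moved, or that delivery has moved, is more likely to pass a test against arm or delivery.

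At stake is a report with two arm results, one bivariate and one adjusted, where a reader may prefer the adjusted one although it is the one that does not estimate the randomized effect.

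**Working it through.** **Inputs from the article.** There are 200 learners (Study Design) allocated 1:1 (Recruitment and Randomization), so 100 per arm. TPB is measured at baseline and 10 weeks, and delivery weekly. The article gives no effect size, SD, alpha or power, so there is no figure to reproduce. **Every effect size below is an assumption**, for a linear model tested at two-sided 5%.

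**Formula.** Let τ be the total effect of arm on delivery, α the effect of arm on the TPB score entered, and β the coefficient of that score in the regression of delivery on arm and TPB. In linear regression:

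adjusted arm coefficient = τ − α × β

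For baseline TPB, α = 0 provided allocation does not alter the baseline answers, so the result is τ. For 10-week TPB, the article itself hypothesizes that α is not zero.

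**Half mediation.** Arm to TPB 0.5, TPB to delivery 0.5, direct effect 0.25. Then τ = 0.25 + 0.5 × 0.5 = 0.50, and the adjusted coefficient is 0.50 − 0.5 × 0.5 = 0.25. In simulation the rejection rate falls from 88% to 40%.

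**Full mediation.** Direct effect 0. Then τ = 0.25, and the adjusted coefficient is 0.25 − 0.25 = 0.

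**Adding an unmeasured common cause**, such as motivation, with weight 0.7 on both TPB and delivery and unit residual variances. Then β = 0.5 + 0.49 / (0.49 + 1) = 0.829.
- Half mediated: 0.50 − 0.5 × 0.829 = 0.09.
- Fully mediated: 0.25 − 0.5 × 0.829 = −0.16. The negative sign comes from the common cause; mediation alone gives 0.

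**Wider settings by simulation** (3,000 runs, 100 per arm, residual SD 0.85, baseline TPB with weight 0.5 on later TPB). Arm to TPB is 0.5 except in the last row. Entries are the mean arm coefficient and rejection rate.

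| Assumed mechanism | Unadjusted | With baseline TPB | With 10-week TPB |
|---|---|---|---|
| Full mediation, total 0.25 | 0.25, 43% | 0.25, 46% | 0.00, 5% |
| Full mediation, total 0.40 | 0.40, 68% | 0.40, 74% | 0.00, 5% |
| Direct 0.15, total 0.40 | 0.40, 82% | 0.40, 84% | 0.15, 22% |
| As above, feedback 0.3 | 0.40, 82% | 0.40, 84% | 0.05, 7% |
| As above, common cause 0.5, no feedback | 0.39, 61% | 0.39, 62% | 0.05, 7% |
| As above, feedback and common cause | 0.40, 63% | 0.40, 64% | −0.04, 7% |
| No mediation, direct 0.40, feedback 0.5 | 0.40, 91% | 0.40, 90% | 0.33, 85% |

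The middle rows show that the adjusted coefficient need not equal even the direct effect: 0.05 where the true direct effect is 0.15.

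**The last row checked by hand.** TPB has no effect on delivery here; delivery raises 10-week TPB with weight 0.5. Given arm, delivery has variance 0.85² = 0.7225, and TPB before feedback has variance 0.25 + 0.7225 = 0.9725.
- β = (0.5 × 0.7225) / (0.9725 + 0.25 × 0.7225) = 0.361 / 1.153 = 0.31.
- α = 0.5 × 0.40 = 0.20.
- Adjusted coefficient = 0.40 − 0.20 × 0.31 = 0.34, against 0.33 simulated.

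The regression thus reports a TPB coefficient of 0.31 where the true effect of TPB on delivery is nil.

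**The case against.** The strongest reply has four parts.

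1. **The harmful model is not stated.** The section names neither the TPB time point nor arm as a term. Baseline scores are an equally plausible choice and would do no harm. If the factors are the TPB measures alone, the model has no arm coefficient to distort. This stands, and it makes the point conditional.

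2. **The arm effect has its own analysis.** The bivariate comparison of delivery is planned separately and is untouched. The regression can be read as a secondary model of what drives delivery, in keeping with the theory. This stands. A reader might infer that the trial's app effect will be adjusted away; the article does not support that, because it nowhere says that the effect is read from the regression.

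3. **The sizes are assumed.** They are. A reader might also infer that an app working exactly as theorized would show a negative effect. Mediation alone does not produce that.

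4. **An article leaves such detail to the full plan.** This is fair for the list of covariates or the handling of mediation as such. It does not dispose of the point, because the article does fix a method: an unadjusted arm comparison, then a significance-screened model that interprets TPB coefficients as impact on delivery. Its own account of TPB as pathway, outcome and end-of-rotation measurement conflicts with that use of the 10-week scores, and the wording lets them in.

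**Conclusion.** The point holds in conditional form. The planned delivery regression does not exclude 10-week TPB, which is the app's pathway, a hypothesized outcome, and measured after the delivery period. If it enters beside arm, the arm coefficient is not the randomized effect. It falls by the mediated part (0.50 to 0.25 at half mediation, to 0 at full mediation) and by more under common causes or feedback. Whether or not arm is in the model, coefficients for 10-week TPB cannot be read as impact on delivery.

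These sizes rest on assumed effects in a linear model and should not be carried over to the logistic model as they stand. The direction of the argument needs only that the app moves TPB and that TPB and delivery are associated within arm. The planned bivariate arm comparison remains valid, so this is a matter of preventing a misleading second result and not a defect in the comparison of delivery between arms.

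**What to change.** Amend the Analyses wording as follows.

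- Estimate the app effect on delivery from a model with arm, training program (the randomization stratifier), placement type and baseline TPB. Fix these terms in advance and do not select them by significance tests.
- State that the app arm completes baseline TPB on the app, after allocation and download but before the tailored recommendations, while controls use Qualtrics. Baseline TPB is therefore not strictly pre-randomization, so add a sensitivity analysis without it.
- Where TPB is to predict delivery, use the baseline score.
- Confine 10-week TPB to a separate analysis labelled exploratory, mediational or associational, stating that it is measured after the outcome period.

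The cost is wording only: every variable named is already collected, and the sensitivity analysis needs no new data. The article reports recruitment as ongoing, so at that stage the change could be made before results.

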## Results

### Beta Testing

Initial results focus on beta testing with student learners from the University of San Francisco School of Nursing. Beta testing was completed in summer 2016. The SUS mean was 65.8 (n=19) which indicates that the SBIRT app is acceptable but needs improvements before rolling out to a larger study sample. Debrief participants reported satisfaction with the Apply and Review sections, which included brief intervention scripts, video demonstrations, the level of detail included in the “Referral to Treatment” section, and inclusion of the PHQ-9 (because this is often required in clinic settings to screen for depression). Suggestions for improvement focused on ease of sign-on and reducing the need for navigation (eg, by having multiple scale items appear on a single screen). These formative beta test data were used for app improvement in preparation for the RCT.

### Randomized Controlled Trial

Enrollment of trial participants began in September 2016 and recruitment is ongoing. Trial results are anticipated to be available in late 2017.

## Discussion

### Principal Findings

The study team found that the TBP model was a useful framework for SBIRT mobile app development and that beta testers responded positively overall to the content and features of the app. The app was developed as a tool to promote translation of substance use screening and intervention skills from classroom to clinical settings. Our intent was to assist in workforce development and promote the broader use of evidence-based interventions to reduce alcohol and drug problems among patients in healthcare and social service settings. We used an app to support SBIRT skill translation, embedded in a TPB-based approach to learning, in order to inform the field regarding how mobile app technology may be used to reinforce pedagogy, improve implementation, and enhance patient care. The app, “UCSF OHN SBIRT App,” has been positively reviewed online [54] and is now publicly available for free downloading (iOS only) via the iTunes store [55] (Figure 5). The RCT in process will determine whether the app has a significant impact on SBIRT skill translation, including rates of SBIRT delivery, learner attitudes, and intent to deliver SBIRT.

Based on the evidence and the need for intervention tools usable across settings to reduce alcohol- and drug-related problems, SBIRT instruction in both graduate training programs and continuing education settings for healthcare professionals has been spearheaded by the US Substance Abuse and Mental Health Services Administration, and training opportunities have expanded rapidly over the past 10 years. If efficacy is demonstrated, the mobile app developed by the study team may serve as a useful tool to improve training for healthcare providers and enhance patient care.

This theory-based mobile app serves as a reference guide, a clinical tool, and a data collection instrument. Learners are expected to complete the initial TPB assessment questions before starting their clinical rotations and are then asked to use the app as often as possible during the course of providing direct care. The reporting function frequency of completion is dependent on the structure of the clinical rotation and the needs of the training program and/or preceptors. Although learners’ use of SBIRT is ultimately limited by what their clinical rotation and preceptor allows, this tool may increase the likelihood of effective SBIRT delivery in healthcare and social service settings. This initial presentation describes our mobile app development process, beta testing, and randomized trial methods, which aim to determine the potential impact of this digital tool.

**Figure 5 figure5:**
[figure not shown]
Icon of the screening, brief intervention, and referral to treatment (SBIRT) mobile app.

### Limitations

The RCT is conducted in the context of graduate training in the schools in nursing, psychology, social work, and medicine, and may not generalize to other types of professional training or to providers learning SBIRT in the context of continuing education. A limitation of the trial methodology that could impact our study results is the inclusion of incentives within the intervention arm for participants to use the app, which likely would not exist in actual clinical settings. In addition, some clinical settings and supervisors may not be support the use of SBIRT, and this could impact a learner’s ability to use the app. Although use of mobile devices is becoming widespread, limitations in access to technology could impact the reach of this tool [36,56]. The app was not designed to integrate responses to screening measures to electronic health records, which could limit its applicability in some clinical settings. Similarly, issues such as adherence to app usage, appropriate use of technology in the workplace, etiquette, and distraction need to be addressed in future studies [57] to effectively integrate mobile apps into health and social service settings.

### Conclusions

In behavioral health, mobile apps have primarily been directed toward patients, including alcohol and drug use reduction [58-61], smoking cessation [62], management of depression [63], and other mental health conditions [64,65]. Our approach is innovative in that it uses a skill translation theory-based intervention to target care providers and improve service delivery for important behavioral health problems. If effective, the mobile app could be scaled-up to reach a wider clinical audience and may be useful in future work on developing models of SBIRT fidelity and broader approaches to improving skill translation.

## Abbreviations

PHQ: Patient Health Questionnaire
RCT: randomized controlled trial
SBIRT: screening, brief intervention, and referral to treatment
SUS: system usability scale
TPB: theory of planned behavior

## Appendix

Multimedia Appendix 5 CONSORT eHealth checklist V1.6.1.
